## Abstract

**Background:**

Calculation of individual risk is the cornerstone of effective cardiovascular prevention. **arriba** is a software to estimate the individual risk to suffer a cardiovascular event in 10 years. Prognosis and the absolute effects of pharmacological and lifestyle interventions help the patient make a well-informed decision. The risk calculation algorithm currently used in **arriba** is based on the Framingham risk algorithm calibrated to the German setting. The objective of this study is to evaluate and adapt the algorithm for the target population in primary care in Germany.

**Methods/design:**

**arriba**-pro will be conducted within the primary care scheme provided by a large health care insurer in Baden-Württemberg, Germany. Patients who are counseled with **arriba** by their general practitioners (GPs) will be included in the **arriba**-pro cohort. Exposure data from the consultation with **arriba** such as demographic data and risk factors will be recorded automatically by the practice software and transferred to the study centre. Information on relevant prescription drugs (effect modifiers) and cardiovascular events (outcomes) will be derived from administrative sources.

**Discussion:**

The study is unique in simulating a therapy naïve cohort, matching exactly research and application setting, using a robust administrative data base, and, finally, including patients with known cardiovascular disease who have been excluded from previous studies.

**Trial registration:**

The study is registered with Deutsches Register Klinischer Studien (DRKS00004633).

## Background

Cardiovascular disease (CVD) is the leading cause of death in industrialized and, increasingly, in developing countries [1]. In 2008, 17.1 million deaths worldwide were caused by cardiovascular disease, which amounts to 30% of all deaths [2]. For Germany, the respective numbers are 342,000 cardiovascular deaths per year (40% of all deaths) [3]. The prevention of cardiovascular diseases is thus an area with high priority.

Within a high-risk prevention paradigm, persons with elevated cardiovascular risk are identified and treated [4]. Here the focus has shifted from the diagnosis and treatment of single risk factors to a view focusing on global cardiovascular risk. On the basis of multivariate algorithms clinicians can now calculate an individual’s cardiovascular risk. Behavioral and pharmacological interventions are offered only to high risk individuals. This approach maximizes absolute risk reduction and efficiency compared to the treatment of individual risk factors [4-6].

 The American Framingham study, starting 1948 and still continuing, has been the first prospective study to identify risk factors contributing to cardiovascular events [7]. From this study the presumably best known and most widely used risk algorithm was derived which was subsequently validated for different populations [8,9]. Although these studies revealed that the Framingham algorithm resulted in an overestimation of the actual observed risk in populations different from the derivation cohort (lack of calibration), its discrimination ability has repeatedly been shown to be excellent [10].

The majority of consultations regarding cardiovascular disease treatment and prevention takes place in primary care [11]. Several tools, most of them based on the Framingham algorithm, are available to support practitioners calculating their patients’ cardiovascular risk. In Germany, **arriba** (http://www.arriba-hausarzt.de) has become the most popular support tool. It has been developed by the Departments of General Practice at Philipps University Marburg and Rostock University. The **arriba** calculator is based on the Framingham risk algorithm with calibration for the German setting. This is achieved by a constant multiplier derived from population cohorts [12]. 10-year absolute risk for cardiovascular events is calculated based on age, sex, blood pressure, lipids, smoking status, family history and diabetes control [13]. For secondary prevention, a simplified estimate is presented based on a prevention trial cohort [14]. Individual risk as well as effects of medication and behavioral change can easily be demonstrated as absolute risk reduction. The software can be freely downloaded by individual general practitioners (GPs).

**arriba** has been designed to be used intuitively. Demonstration of effects of single intervention and their combinations does not require sophisticated understanding of absolute and relative risk reduction. **arriba** thus supports shared decision-making between physician and patient as well as adherence to treatment plans [15,16]. **arriba** has been evaluated in a cluster randomized controlled trial, in which patient satisfaction, participation, and change in cardiovascular diseases risk status were investigated. It could be shown that patients randomized to the intervention group had a significant higher satisfaction with process and result than controls [17]. The acceptance by **arriba** among primary care physicians varied, depending on their personal motivation, their attitude towards shared decision-making in general and context variables such as time constraints [18].

Since 2004, primary care in Germany has increasingly been provided within gatekeeping schemes (Hausarztzentrierte Versorgung – HzV). In the German federal state Baden-Württemberg **arriba** has been implemented as part of the HzV of the Allgemeine Ortskrankenkasse Baden-Württemberg (AOK BW), the largest statutory non-profit health insurance in the federal state Baden-Württemberg, Germany [19]. Regular automated data transfer and consent by patients who participate in the HzV has provided the opportunity to establish a cohort to improve the **arriba** risk algorithm.

The study we are presenting here has as its objective the validation and adaptation of the **arriba** risk algorithm for future use in primary care. We will not only address primary prevention, but also prediction for patients with known cardiovascular disease and/or diabetes mellitus.

## Methods/design

**arriba**-pro is a prospective, longitudinal cohort study based on medical and administrative data provided by primary care practices and a large health insurance company. Attending patients who enrolled in the HzV AOK BW and are counseled with **arriba** by their GPs are eligible.

### Participants and recruitment

In the Land of Baden-Württemberg (BW), about 1 million members of the insurance company AOK BW are voluntarily enrolled in the HzV AOK BW. 3,500 out of 7,100 GPs in BW have registered to provide primary care services for these patients. For all GPs providing HzV services specially designed software for documentation and billing is available, including the **arriba** software. Every patient enrolled in the HzV-scheme for who **arriba** is used can automatically be included into the study after the approval of his/her GP.

### Exposure, outcomes and effect modifiers

Exposure variables will include demographic data and cardiovascular risk factors (see Table 1).

**Table 1 T1:** Exposure variables

Demographics	Age/year of birth
	Gender
	Insurance number
Cardiovascular risk factors	Total Cholesterol mmol/L or mg/dL
	HDL-Cholesterol mmol/L or mg/dL
	Smoking yes/no
	Systolic blood pressure mm Hg
	Patient on blood pressure lowering medication yes/no
	Diabetes yes/no
	Diabetes control glycosylated hemoglobin
	Known atherosclerotic disease yes/no
	Family history for cardiac disease yes/no

Acute coronary syndrome (fatal/non-fatal) and acute stroke (fatal/non-fatal), excluding transient ischaemic attacks, will be the main outcome of the study. Secondary outcomes will be overall death, hospitalization for cardiovascular disease, any hospitalization, revascularization procedures (coronary and/or carotid vascular beds), and outpatients’ cardiology consultations. The occurrence of these will be determined from administrative data (see below). Drug treatment prescribed after recruitment into the study will be analyzed as potential confounder or effect modifier.

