### Data analysis

The main purpose of the analysis is the validation and adaptation of the risk algorithm presently implemented in the **arriba**-software [20]. The current algorithm is based on the Framingham cohort and is calibrated to German populations. Exposure variables are limited to the set currently recorded by the **arriba**-software (see Table 1). As a result of our study we will be able to adjust their weights (coefficients) as well as the intercept (base risk), possibly identify predictors that contribute little and can thus be omitted, and specify interactions between predictors.

We will use a stepwise procedure to analyze the data, going from the mere descriptive analysis to the univariate- and multivariate analysis, using the appropriate tools in each step.

Among the predictors to be entered into the multivariate model are time-independent variables, such as sex or previous cardiovascular disease, but also time-dependent factors, such as medication modifying cardiovascular risk. For pragmatic reasons, cholesterol and blood pressure levels will be regarded as time-independent since they are either relatively stable characteristics (LDL-/HDL-cholesterol) and/or cannot be measured over time within the current study design (blood pressure, smoking status). However, data on risk-modifying medication (e.g. statins, blood-pressure lowering drugs) can be retrieved from the AOK BW and be entered into the model. Treatment is likely to change over time but this can be accommodated in the statistical model.

To adjust for the confounders mentioned above, an extension of the Cox Proportional Hazards Model for time-dependent variables will be used as suggested by Kleinbaum [21]. To simulate a therapy naïve cohort, drug treatments will be adjusted for. The statistical analysis will be performed by the universities of Rostock und Marburg with support of the Department of Medical Biometry and Epidemiology, Hamburg.

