## Discussion

The main aim of the cohort study outlined here is the validation and adaptation of a cardiovascular risk algorithm.

Cardiovascular risk algorithms have repeatedly been shown to have limited predicting power when tested on independent samples [10,23]. There are many reasons for this unsatisfactory state, among these biological variability, demographic, social, and cultural differences between derivation and validation cohorts, comorbidities, and intervention by health care providers outside the study protocol, to name just a few.

Our study does address three of these in an innovative way:

Simulation of a therapy-naïve cohort: The main goal of the **arriba** risk calculator is the unbiased information of individual patients in primary care practice. For individuals considering long-term interventions such as lipid or blood-pressure lowering therapy, predictive evidence should be based on cohorts without interventions modifying cardiovascular risk. However, this is unfeasible since most subjects in the cohort will be treated by their health care provider once a single risk factor or their global cardiovascular risk is found to be elevated. By accommodating drug therapy during follow-up we will be able to simulate a therapy-naïve cohort and thus provide risk estimates not biased by pharmacological interventions. To our knowledge this has not been attempted before.

Match between research and application setting: Previously developed cardiovascular risk algorithms were derived from geographically or occupationally defined populations. This puts a limit on their generalizability regarding counseling of individual patients in primary care. Our study sample, however, is drawn from exactly the population for which the algorithm will be used once the study is completed.

Inclusion of patients with known cardiovascular disease: Previously published risk algorithms were derived from populations free of overt cardiovascular disease. They can thus not be used to inform decision-making for secondary prevention. Against the background of aging populations with high prevalence of cardiovascular disease, this is a serious limitation. As a result of our study, a risk calculator applicable to this group will be available.

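### Treatment already in place at recruitment is largely outside the stated drug adjustment, so the therapy-naive risk claim is unsupported for patients treated at entry

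*Protocol article*

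**What the plan says.** All references are to the protocol article.

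- **Drug window.** Exposure, outcomes and effect modifiers states: "Drug treatment prescribed after recruitment into the study will be analyzed as potential confounder or effect modifier". The Discussion uses the same window for its leading innovation: "By accommodating drug therapy during follow-up we will be able to simulate" a therapy-naive cohort. It concludes that the resulting risk estimates will be free of bias from drug treatment.
- **No window.** Data analysis says that "data on risk-modifying medication (e.g. statins, blood-pressure lowering drugs) can be retrieved from the AOK BW and be entered into the model". It adds that drug treatments will be adjusted for in an extended Cox model with time-dependent covariates. Neither statement is limited to the period after recruitment.
- **Who enters.** Methods/design makes eligible "Attending patients who enrolled in the HzV AOK BW and are counseled with" arriba. No one is excluded for being on treatment. The Background extends the aim beyond primary prevention, "but also prediction for patients with known cardiovascular disease and/or diabetes mellitus".
- **Baseline drug information.** Table 1 has one item: "Patient on blood pressure lowering medication yes/no". It has none for statins, antiplatelet or glucose-lowering drugs. Data analysis closes the set: "Exposure variables are limited to the set currently recorded by the" arriba software.
- **Risk-factor values.** "For pragmatic reasons, cholesterol and blood pressure levels will be regarded as time-independent". No correction for treatment at the time of measurement is stated.

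**The concern.** The study wants to tell an untreated person what the risk is without drugs. For a patient who starts a statin after recruitment, baseline cholesterol is an untreated value and the time-dependent drug term can carry the drug effect. For a patient already on a statin, baseline cholesterol has been lowered by the drug. Setting the drug term to zero while keeping that value does not give the untreated risk, because the part of the effect that acts through cholesterol stays in the predictor. The prediction for such a patient is then too low.

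Without prescriptions from before recruitment, the first refill of a long-standing user also looks like a new start. A drug term that does not separate the groups would blend two quantities: the full drug effect in new users, and the effect left over after conditioning on an on-treatment value in prevalent users. The base risk and risk-factor weights, which the study sets out to re-estimate, come from the same mixture.

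**Working it through.** **1. Which patients the stated rule handles**

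| Patient at recruitment | Baseline drug status in the exposure set | Baseline value | Captured by prescriptions after recruitment |
|---|---|---|---|
| Untreated, starts later | Not needed | Untreated | Yes, from the start of treatment |
| Already on a blood-pressure drug | Yes (Table 1) | On-treatment pressure | From the next prescription |
| Already on a statin | No | On-treatment cholesterol | From the next prescription, indistinguishable from a new start |
| Already on an antiplatelet or glucose-lowering drug | No | Glycosylated hemoglobin on treatment, for the latter | From the next prescription, indistinguishable from a new start |

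The rule works for the first row. In the second, the Table 1 item lets the model tell treated from untreated pressure values, although no such use is stated. The last two rows are not resolved.

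**2. Size of the omitted-drug part**

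The documents give neither the share p treated at recruitment nor a drug effect, so both are assumptions: p = 10-50%, hazard ratio (HR) 0.6-0.8. If baseline treatment were ignored for the whole follow-up, then

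mean hazard / untreated hazard = (1 - p) + p × HR = 1 - p(1 - HR).

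- p = 0.10, HR = 0.8: 1 - 0.10 × 0.2 = 0.98, understated by 2%.
- p = 0.30, HR = 0.7: 1 - 0.30 × 0.3 = 0.91, understated by 9%.
- p = 0.50, HR = 0.6: 1 - 0.50 × 0.4 = 0.80, understated by 20%.

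Refills remove some of this. The separate distortion from on-treatment risk-factor values is not in these figures and cannot be computed from the documents.

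**3. Whether the sample can carry the fix**

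The protocol's own figures reproduce under its rule of 10 events per predictor:

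- Main analysis: 9 × 10 / 0.05 = 1,800.
- Known coronary heart disease: 9 × 10 / (0.10 × 0.30) = 3,000 in total.
- Projected enrolment if the pace holds: 4,100 / 2 × 4 = 8,200.

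Assume three drug classes:

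- One baseline term each, 12 predictors: 120 / 0.05 = 2,400 and 120 / 0.03 = 4,000.
- A baseline term plus one interaction each, 15 predictors: 150 / 0.05 = 3,000 and 150 / 0.03 = 5,000.

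Both fit within 8,200.

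An analysis restricted to patients untreated at recruitment divides the minimum by (1 - p). For p = 10%, 30% and 50%, the 1,800 becomes 2,000, 2,572 and 3,600. For the coronary subgroup, with p now the treated share within it, the 3,000 becomes 3,334, 4,286 and 6,000; at p = 70% it is 10,000, above 8,200. The break-even is 1 - 3,000 / 8,200 = 63%. These counts use the protocol's 10-year risks, so they presume ten years of follow-up; funding covers a five-year study.

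**The case against.** The strongest reply is that the text never excludes earlier drugs. Data analysis, which governs the model, has no time limit, and the drug coding may sit in an analysis plan that is not shown. This stands in part. A reader might infer that only drugs prescribed after recruitment are used, but the Table 1 blood-pressure item and the open wording of Data analysis do not support that. What remains is that two sections state a follow-up window, one does not, and the claim of unbiased estimates is built on the window.

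Second, continuing users refill, and the time-dependent model then counts them as treated. This also stands. It makes the percentages above a ceiling for the omitted-drug part. It does not recover the pre-treatment cholesterol or pressure, nor show who was already treated.

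Three further inferences go beyond the documents:

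- **Blood-pressure drugs counted twice.** The Table 1 item is status at the consultation and the claims variable is later treatment. Nothing fixes that both stay in the final model. Their relation is simply not stated.
- **A therapy-naive calculator promised for known disease.** The Discussion lists the simulation and the inclusion of known disease as separate innovations. For the latter it promises a calculator applicable to that group.
- **The authors think the cohort is untreated.** They say an untreated cohort is not feasible and propose to simulate one.

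**Conclusion.** The point holds in limited form. For patients treated at entry, the stated approach neither restores untreated risk-factor levels nor separates prevalent from new use, so the Discussion's claim of estimates unbiased by drug treatment is not supported for them. It should be corrected because that claim is one of the three innovations on which the study is justified. It does not threaten feasibility.

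The actual bias is unknown. The 2-20% range rests on the assumed treated share and hazard ratio and on baseline treatment being ignored throughout; it is not an expected bias. If a full analysis plan already specifies a look-back and the handling of on-treatment values, what remains is to align the article's wording with it.

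**What to change.** 1. Reconcile Exposure, outcomes and effect modifiers, Data analysis, and the Discussion on one drug window that includes a look-back before recruitment, for example 12 months. Data collection already provides for querying the insurer for treatments, so this extends the date range, provided that earlier claims are available for these patients.
2. Classify each drug class at recruitment as prevalent, new or no use.
3. Let the model distinguish risk-factor values measured on and off treatment, through a baseline-treatment term with an interaction. Alternatively, add a sensitivity analysis in patients untreated at recruitment.
4. State how the Table 1 blood-pressure-drug item relates to the claims variable.
5. Limit the therapy-naive claim to groups with adequate untreated person-time, and report that person-time by group.

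The cost is a wider data query, some extra covariates, and a therapy-naive estimate resting on fewer patients. Under the protocol's own rule the projected sample can carry the extra covariates. In known coronary disease an untreated-only analysis may be too small.

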### Data collection

During a consultation supported by **arriba** GPs will enter the patient’s age, sex, cardiovascular risk factors and the interventions that have been discussed with the patient. These data together with the calculated absolute cardiovascular risk will automatically be stored within the **arriba** software. GPs will always be asked for their approval regarding each patient’s **arriba** data being stored by the software and transferred for further processing. Data will be regularly transferred to the central computing centre. From there the data will be sent to an independent clinical trial centre (CTC North at University Medical Center Hamburg Eppendorf). The CTC North will provide data files to the collaborating departments at the universities of Marburg and Rostock. These will include clinical data and pseudonymised identifiers for patients and GPs (see Figure 1).

**Figure 1 F1:**
[figure not shown]
Data-transmission and pseudonymisation steps.

Much care will be taken to preserve the confidentiality of data from **arriba** counselling. Patients ID-numbers will be pseudonymised with the key known only to AOK BW. Clinical data will be encrypted so that only the participating academic researchers will be able to read them. At the CTC North GPs identifiers will also be pseudonymised. The pseudonymisation procedure will allow to link information of the same patient from different data sources while also maintaining full confidentiality and privacy of patients’ and GPs’ data.

In order to obtain information on outcome and treatments for participating patients, the AOK BW central database will regularly be queried. The resulting data will be provided to the academic departments at the universities of Marburg and Rostock via CTC North with all the precautions regarding confidentiality described above. These data will also include diagnostic codes, such as cardiovascular events, and relevant vascular procedures, such as percutaneous coronary interventions or coronary bypass surgery (see Figure 2).

**Figure 2 F2:**
[figure not shown]
Data-matching and pseudonymisation steps.

### Data analysis

The main purpose of the analysis is the validation and adaptation of the risk algorithm presently implemented in the **arriba**-software [20]. The current algorithm is based on the Framingham cohort and is calibrated to German populations. Exposure variables are limited to the set currently recorded by the **arriba**-software (see Table 1). As a result of our study we will be able to adjust their weights (coefficients) as well as the intercept (base risk), possibly identify predictors that contribute little and can thus be omitted, and specify interactions between predictors.

We will use a stepwise procedure to analyze the data, going from the mere descriptive analysis to the univariate- and multivariate analysis, using the appropriate tools in each step.

Among the predictors to be entered into the multivariate model are time-independent variables, such as sex or previous cardiovascular disease, but also time-dependent factors, such as medication modifying cardiovascular risk. For pragmatic reasons, cholesterol and blood pressure levels will be regarded as time-independent since they are either relatively stable characteristics (LDL-/HDL-cholesterol) and/or cannot be measured over time within the current study design (blood pressure, smoking status). However, data on risk-modifying medication (e.g. statins, blood-pressure lowering drugs) can be retrieved from the AOK BW and be entered into the model. Treatment is likely to change over time but this can be accommodated in the statistical model.

To adjust for the confounders mentioned above, an extension of the Cox Proportional Hazards Model for time-dependent variables will be used as suggested by Kleinbaum [21]. To simulate a therapy naïve cohort, drug treatments will be adjusted for. The statistical analysis will be performed by the universities of Rostock und Marburg with support of the Department of Medical Biometry and Epidemiology, Hamburg.

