### Sample size

In the main analysis, we aim to validate and re-calibrate the risk algorithm implemented in the **arriba**-software for primary prevention. To quantify the impact of a predictor, at least 10 events are needed [22]. If we assume patients in our cohort to have an average risk of a cardiovascular event of 5% in 10 years, the study of 9 predictors (see Table 1) would require a sample of at least 1,800 patients. However, further analyses will require a higher sample size. To validate the risk algorithm within the subgroup of patients with a known coronary heart disease a total sample size of 3,000 patients would be required if we assume that the percentage of this subgroup is 10% of the total sample and that the average risk of a cardiovascular event within this group is 30% in 10 years. Adjusting for the risk-modifying effect of treatment will raise the number of covariates to be entered in the models and the sample size accordingly. Within the first two years, 466 GPs have recruited about 4,100 patients. Considering a total time of enrolment of 4 years, the resulting sample size will meet our requirements with a sufficient safety margin.

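### Adjusting for cohort-estimated drug terms in a time-dependent Cox model does not secure the claim that the therapy-naive risk is free of treatment bias

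*Protocol article*

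**What the plan says.** All references are to the protocol article.

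- **Data analysis, method.** The stated route to an untreated risk is covariate adjustment: "To simulate a therapy naïve cohort, drug treatments will be adjusted for". The model is named: "an extension of the Cox Proportional Hazards Model for time-dependent variables will be used". Prescription data "can be retrieved from the AOK BW and be entered into the model".
- **Sample size.** "Adjusting for the risk-modifying effect of treatment will raise the number of covariates to be entered in the models". Treatment terms are thus ordinary covariates with coefficients estimated in this cohort. No external treatment effect is named.
- **Data analysis, risk factors.** "cholesterol and blood pressure levels will be regarded as time-independent". Part of the reason given is that some factors "cannot be measured over time within the current study design (blood pressure, smoking status").
- **Discussion, why treatment starts.** An untreated cohort is called unfeasible because "most subjects in the cohort will be treated by their health care provider once a single risk factor", or their overall risk, turns out to be raised.
- **Discussion, claim.** Accommodating drug therapy during follow-up is said to "provide risk estimates not biased by pharmacological interventions".
- **Discussion, limitations.** These cover smoking measured only at baseline, other behavioural factors and the restricted predictor set. Confounding of treatment is not among them.

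**The concern.** Letting a drug term vary over time handles when a patient was treated. It does not handle why. If a prescription is prompted by something prognostic that the baseline covariates do not carry, such as a later rise in blood pressure, the drug coefficient picks up that extra risk along with the drug's effect. The estimated hazard ratio then moves towards or above 1. Predicting with the drug term at zero returns the risk of those who stayed untreated, not the risk everyone would have had without treatment.

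The therapy-naive simulation is the first of the three innovations in the Discussion. The Background says the software shows patients their individual risk and the absolute effect of medication. An error in the base risk would carry into both displays.

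**Working it through.** **The plan's own figures.** With 10 events per predictor and 9 predictors, 9 × 10 / 0.05 = 1,800. For the coronary heart disease subgroup, 9 × 10 / 0.30 / 0.10 = 3,000. Both reproduce exactly, and the present point does not rest on them.

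**Closed form.** Let f be the share of person-time treated, h the true drug hazard ratio, and c the ratio of *untreated* hazard in treated to untreated person-time, given the modelled covariates. Write λ for the hazard in untreated person-time.

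- True therapy-naive rate: λ[(1 − f) + f·c]
- Estimated drug hazard ratio: c·h
- Estimated therapy-naive rate (drug term at zero): λ
- Estimated / true: 1 / [(1 − f) + f·c]

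The documents give none of f, c or h. With h = 0.7 assumed and a true therapy-naive risk of 5% (the average risk in the Sample size section, used here only as a scale):

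| f | c | estimated HR | ratio | 5% is estimated as |
|---|---|---|---|---|
| 0.2 | 1.2 | 0.84 | 1/1.04 = 0.962 | 4.8% |
| 0.4 | 1.5 | 1.05 | 1/1.20 = 0.833 | 4.2% |
| 0.6 | 2.0 | 1.40 | 1/1.60 = 0.625 | 3.1% |
| any | 1.0 | 0.70 | 1 | 5.0% |
| 0.2 | 0.8 | 0.56 | 1/0.96 = 1.042 | 5.2% |
| 0.6 | 0.8 | 0.56 | 1/0.88 = 1.136 | 5.7% |

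The sign of the error depends only on whether c is above or below 1.

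**Simulation.** One run per scenario: 120,000 patients, 10 years in quarter-year steps, true drug hazard ratio 0.7. The Cox model holds the baseline risk factor and a time-dependent drug term. The 10-year risk predicted with the drug term at zero is compared with the true untreated risk. In every scenario 52 to 61% of patients had been started on the drug by year 10.

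| Why treatment starts | estimated HR | estimated risk | true risk | error |
|---|---|---|---|---|
| At random (control) | 0.74 | 5.13% | 5.04% | 2% high |
| Measured baseline value only | 0.70 | 4.14% | 4.06% | 2% high |
| Current value, moderate drift | 0.92 | 3.84% | 4.40% | 13% low |
| Current value, strong drift | 1.66 | 3.32% | 5.54% | 40% low |
| Healthy-user selection only | 0.49 | 6.02% | 5.38% | 12% high |
| Healthy-user selection and moderate drift | 0.54 | 5.21% | 4.72% | 10% high |

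The control row shows that differences of about 2% are within what a single run can produce. The drift settings are not small: moderate means 0.15 baseline standard deviations per quarter, or 0.15 × √40 = 0.95 by year 10. Strong means 0.30 × √40 = 1.90.

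**The case against.** The strongest reply is that nothing in the article says changes *after* baseline trigger treatment. Risk factors and global risk are entered and calculated at the **arriba** consultation, and those values are in the model. If prescribing follows them, the bias all but vanishes (4.14% against 4.06%). The article also calls cholesterol relatively stable. This stands as a condition on the size of the bias. It does not rescue the claim, because the article neither states nor defends the assumption that baseline values capture all prognostic reasons for prescribing over years of follow-up.

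Second, the claim concerns bias from drug treatment, within an openly labelled simulation. It is not a claim of no bias at all. That is fair, but it is exactly this narrower property that the method leaves unsecured.

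Third, a condensed article may leave weighting and sensitivity analyses to an analysis plan. That is true, and their absence is not the point. The article fixes the method and states a property for its result.

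Three stronger readings are tempting and not supported:

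- *The estimates will be too low.* Healthy-user selection reverses the sign in the table above.
- *There are too few events to estimate drug effects.* This depends on follow-up. Doubling the 4,100 patients recruited in two years gives 8,200, of whom 90% (7,380) would be primary prevention. Over 10 years at 5% that is 369 events. With half the person-time treated, SE(log HR) = 1/√(369 × 0.25) = 0.104, so the 95% interval around 0.75 is about 0.61 to 0.92. A wide interval arises only if follow-up stops at the funded five years: with an assumed mean of 3 years, about 113 events give SE 0.188 and about 0.52 to 1.08. The article itself calls short follow-up preliminary and seeks more.
- *Drug effects must not be estimated in the cohort.* Estimating them is a trade-off, not an error in itself.

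**Conclusion.** The concern holds in a limited form. The article fixes a method that leaves any indication not captured by the baseline values inside the drug coefficient, then describes the result as free of bias from drug treatment and omits the issue from its limitations. The description should change and a companion analysis should be added.

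Given the article's own account of why patients are treated, downward bias is the most plausible direction. Its size cannot be established from the document. The illustrations run from nothing material, through 13 to 40% too low, to 10 to 12% too high. All of them rest on an assumed hazard ratio, drift, prescribing pattern and 10-year follow-up. No arithmetic in the article is wrong on this point.

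**What to change.** 1. Keep the cohort-estimated drug terms, and pre-specify alongside them an analysis in which treated person-time enters as a fixed offset: log hazard = baseline + predictors + A(t) × log(HR external), with A(t) the treatment indicator. The external relative effects could be those behind the software's displayed medication effects, if suitable. Run it over a stated range.
2. Report how far the therapy-naive base risk moves between the two analyses and across the range.
3. In the Discussion, describe the estimates as *corrected, under stated assumptions, for pharmacological interventions*.
4. Add confounding by indication to the limitations.

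Under the closed form, the offset estimate relative to the truth is [(1 − f) + f·c·h] / {[(1 − f) + f·H]·[(1 − f) + f·c]}, where H is the external hazard ratio used. For f = 0.4, c = 1.5 and h = 0.7, a correct H of 0.70 gives 1.02 / (0.88 × 1.20) = 0.966, against 0.833 with the free coefficient. An H of 0.75 gives 1.02 / (0.90 × 1.20) = 0.944. In this example the offset reduces the error but does not remove it.

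Censoring at treatment start with inverse-probability weights is optional. It is limited by the same lack of updated risk factors.

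The cost is analysis-plan wording and a few days of programming, with no new patient data. The downside is that the offset assumes external effects and adherence carry over to this cohort, which the stated range puts on display.
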